## Abstract

**Introduction and objectives::**

Mandible reconstruction with vascularized fibula flap is the standard treatment for segmental mandibulectomy in patients with tumor or trauma. But the height of the fibula graft is insufficient for dental implant placement and prosthetic rehabilitation to replace the missing teeth, which in turn will compromise the functional efficiency and aesthetics of the patient. Although the bone height can be augmented through onlay grafting with iliac crest, it is associated with limitations like donor site morbidity and fast resorbability. This suggests the need for a synthetic biomaterial for vertical bone augmentation in implant dentistry.

We have developed a biomimetic, porous, mechanically stable, and biodegradable nanocomposite named “NANOTEX BONE Graft” and its bone regeneration potential was evaluated in pre-clinical animal models. In this clinical trial, the safety as well as the efficacy of NANOTEX to augment new bone over fibula and further its ability to integrate with dental implants will be studied. The study has received the approval of the Ethics Committee of Amrita Institute of Medical Sciences and Central Drugs Standard Control Organization (CDSCO), India.

**Methods::**

We have designed a prospective, single-center, non-randomized pilot clinical study. Patients with benign tumor or trauma indicated for mandibular reconstruction followed by implant rehabilitation will be included in the study. Eligible patients will be enrolled after obtaining informed consent. The study will be initiated and followed up as per defined timelines.

**Highlights:**

## 1. Background

### 1.1. Introduction

According to the Union of International Cancer Control Report, the annual incidence of head and neck cancers worldwide is more than 5,50,000, and 90% of this includes the oral cavity [1]. India fact sheet of GLOBOCAN 2020 reports that oral cancers have the second most incidence (10.3%) with 1,35,929 new cases and 8.8% mortality yearly [2]. The International Agency for Cancer Research has predicted that India’s incidence of oral cancer will rise to more than 1.7 million in 2035 [3] due to increased usage of tobacco chewing. Cancer Statistics in India (2018) shows oral cancer as the leading cause of mortality in men, and it is responsible for 25% of cancer-related deaths [4]. World Health Organisation (WHO) report on the global frequency of benign and malignant odontogenic tumors presented that the incidence of tumors affecting the mandible is double that of the maxilla (2.8:1). The benign odontogenic tumors constitute a major percent (95.7%) than the malignant tumors (4.3%), among which ameloblastoma accounts for 30.6% [5]. Treatment of these tumors necessitates surgical removal of the jaw bone, but the resection (either segmental or marginal) leaves the patient with functional impairments like difficulty in mastication, deglutition, and speech along with aesthetic defects like loss of continuity, contour, bone height and width [6].

Vascularised free fibula is the standard autograft used for mandibular reconstruction. Further, Titanium dental implants will be placed to the fibula for dental rehabilitation as it serves as an artificial analog of the missing teeth. This in turn enhances the quality of the patient’s life by improving the masticatory efficiency and aesthetic outcome [7]. Nevertheless, there is a height discrepancy between the native mandible and transplanted fibula, restricting the placement of dental implants [8]. The compromised implant length due to reduced vertical bone height can lead to an improper implant crown root ratio. In addition, an increased prosthetic height to achieve the occlusal plane level will lead to implant overloading and failure of the prosthesis. This necessitates the need for vertical bone augmentation in the fibula reconstructed mandible. Surgical techniques like double-barrelling and vertical distraction osteogenesis can increase bone height, but those techniques are complicated [9]. Onlay grafting using iliac crest (placement of graft on the fibula and its fixation with screws) is another option, but it has drawbacks such as high resorption rate and donor site morbidity [10]. Hence, there is a need for an efficient biomaterial to be placed over fibula, which can promote bone regeneration and increase the bone height. An ideal biomaterial should provide an extracellular matrix microenvironment that mimics the natural bone in regulating cell and tissue behavior. In load-bearing regions like mandible, the strength of the scaffold is also significant in providing signals for bone remodeling. This material also has to accept titanium implant placement. At present, there is no synthetic block graft available for intra-oral bone augmentation purposes to satisfy all these needs.

### 1.2. Rationale

Natural bone is principally a fibrous composite, consisting of inorganic (60–65wt% nanohydroxyapatite (nanoHA) as well as various trace elements like Na, Mg, K, Sr, Zn, Ba, Cu, Fe, and Si) and organic phase (30–35% collagen fibrils). Many synthetic biomaterials like nanoHA, nanoHA composites and Si-HA are widely used in clinics for orthopaedic and dental applications because of their chemical and crystallographic similarity to bone apatite. Still, none of them was found suitable for bone augmentation and Ti dental implantation [11,12,13].

NANOTEX BONE Graft is a fibrous composite that mimics native bone and is made of silica-nanoHA-gelatin with poly L(Lactic acid) (PLLA) fibers [14]. The incorporation of fibers in silica-nanoHA-gelatin matrix can enhance mechanical strength and allow handling during surgical implantation. It is porous (pore size ranges between 50–350 um) and osteoconductive, promoting the infiltration and proliferation of stem cells and osteogenic cells. Besides, it enhances the osteogenic differentiation of mesenchymal stem cells. The material has also been shown to promote the expression of vascular endothelial growth factor, resulting in enhanced endothelial functionality and angiogenesis, a process that is important for new bone formation [15]. Preclinical studies performed in rabbit and pig models proved its ability to promote new bone formation in critical-sized mandible defects through the normal bone healing process. In parallel to bone tissue regeneration, better biodegradation was noted for nanocomposite fibrous scaffold and its biodegradation rate was in par with new tissue formation. More importantly, the newly formed bone could efficiently integrate with Ti dental implants, which was demonstrated in pre-clinical studies [16,17,18].

### 1.3. Study Objectives

The primary objective of this study is to evaluate the safety of the NANOTEX BONE Graft in combination with the fibula flap implanted at segmental mandibulectomy defects. The secondary objective is to evaluate the efficacy of the NANOTEX BONE Graft in bone regeneration when augmented on the fibula and Titanium dental implant integration.

## 2. Methods

### 2.1. Study design

Prospective, single-center, non-randomized pilot clinical study.

### 2.2. Study setting

Amrita Institute of Medical Sciences, Kochi, India. The study treatment duration is expected to be 12 months.

### 2.3. Study intervention

NANOTEX BONE (Nanocomposite Fibrous Scaffold), is a mechanically strong, porous, biodegradable scaffold with bone regeneration properties.

### 2.4. Study participants

Subjects of both genders with 18–65 years of age suitable for mandible reconstruction resulting from tumor resection or trauma.

### 2.5. Eligibility criteria

Inclusion and exclusion criteria are summarized in Table 1.

**Table 1 T1:** Inclusion and exclusion criteria.

INCLUSION CRITERIA	EXCLUSION CRITERIA

Patients must be 18 to 65 years of age while signing the informed consent.	Uncontrolled alcohol, tobacco, or substance abuse within 6 months before implantation

Segmental mandibular defect due to benign tumor resection or trauma	Patients indicated for radiotherapy before and after surgery

A female patient who is neither pregnant nor breastfeeding	Mandibular ramus defects with open wounds

A patient who can report to the study center at defined timelines throughout the study duration	Active uncontrolled infection or malignancy

Patients whose clinical laboratory test results are within the reference range for healthy individuals, or where outside the reference range are judged as not clinically relevant by the Investigator	Systemic disease that would affect the surgical procedure or implant integration including uncontrolled diabetes, osteoporosis, rare bone disorders like osteopetrosis, or any other metabolic bone disease

	Conditions like inherited coagulopathies or bleeding disorders that may affect the implant success or cause post-operative complications

	Increased alkaline phosphatase, increased serum calcium, or Vitamin D deficiency. Oral bisphosphonate or the use of systemic steroids or anabolic agents (e.g., teriparatide) for osteoporosis treatment.

	Patients with inadequate donor sites for lipoaspirate of adipose tissue

	Mixed connective tissue diseases and collagen diseases that can result in poor wound healing after surgery

### 2.6. Sample size

Assuming the level of significance as 5%, the incidence rate of adverse events as 3%, and the margin of error as 10%, the study will be done in 10 subjects to estimate the safety and efficacy with enough precision.

### 2.7. Allocation

Subjects are considered enrolled in the study upon signing the Institute Ethics Committee approved Informed Consent Form (ICF). Informed consent will be obtained before performing any of the study-related procedures or entering any subject data in the Case Report Form. The patient will be given adequate information about the study and sufficient time to comprehend the information in the IC Form before deciding to participate in the study. The study center will be responsible for maintaining subject identification records (Eg. Subject identification log).

### 2.8. Study procedure and data collection

*NANOTEX BONE graft augmentation on fibula*: A patient who is undergoing segmental mandibulectomy due to benign tumor or trauma will be included in the study after obtaining the consent. Pre-operative planning of the surgery includes virtual surgical planning and model surgery to determine the most ideal position of the fibula and NANOTEX BONE graft. Further, the mandible will be resected followed by free fibula flap reconstruction, which will be stabilized using plates and screws and anastomosed with host vessels as per standard protocol. Further, the height of the fibula will be augmented by placing the scaffold over the fibula and fix with screws and a plate. The size of the block graft will vary depending on the size of the patient defect and fibula. The skin paddle of the fibula flap will be inset to close the mucosal defect over the scaffold and fibula. Post-operative care will be taken as per standard clinical practice for fibula reconstruction.*Implant placement and Prosthetic rehabilitation*: The procedure for implant placement involves reconstructed site preparation and implant insertion. The number and size of titanium dental implants will be planned based on bone gain. The loading of the implant (prosthesis placement) will be done if the implant is integrated well with the bone.

### 2.9. Timelines/Participant follow up

Clinical data will be collected at the Screening Visit, Surgery Period (Day 1- Day 10), Follow up Visit (1 month and 3 months), Titanium Implant placement (6 Months), Prosthesis placement (9 months), and End Follow up Visit (12 Months).

### 2.10. Outcome Analysis

#### Primary outcome

*Safety of NANOTEX BONE Graft*: The adverse events will be assessed by 3 parameters: Inflammation, wound dehiscence, and discharging sinus. The assessment will be done at all time points and scores will be given for each category.

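### The primary safety outcome counts only three local wound signs, so loss of the flap or graft, fixation failure or re-operation without such a sign is not an event

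*Protocol article*

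**What the plan says.** Section 1.3 of the Protocol article gives the primary objective as to "evaluate the safety of the NANOTEX BONE Graft in combination with the fibula flap", implanted at segmental mandibulectomy defects. Appendix A repeats the combination of graft and flap in the primary outcome entry.

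Section 2.10 (Primary outcome) turns this into a measurement: "The adverse events will be assessed by 3 parameters: Inflammation, wound dehiscence, and discharging sinus". It continues: "The assessment will be done at all time points and scores will be given for each category".

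Section 2.9 gives the time points. After screening they are "Surgery Period (Day 1- Day 10), Follow up Visit (1 month and 3 months), Titanium Implant placement (6 Months), Prosthesis placement (9 months"), and a final visit at 12 months.

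Section 2.6 sizes the study on one proportion. It takes "the incidence rate of adverse events as 3"%, "the margin of error as 10"% and a 5% significance level, and concludes that "the study will be done in 10 subjects to estimate the safety and efficacy with enough precision". It does not say which events the 3% covers.

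**The concern.** The objective concerns a construct of graft plus flap, and the outcome concerns the state of the wound. Section 2.8 describes what the construct consists of: a free fibula flap joined to host vessels and held by plates and screws, with the scaffold fixed on top by screws and a plate. The most serious ways in which it can fail are loss of the flap, loss or removal of the scaffold, failure of the fixation, and a return to theatre. None of these is an event under section 2.10 unless inflammation, dehiscence or a sinus is also scored.

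This is the primary outcome of a first clinical study of the material, with 10 patients and no control arm described. One uncounted major failure would be one patient in ten. A primary result of no events could then stand beside a lost flap or a removed scaffold and read as reassurance that the data do not give.

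**Working it through.** **Step 1. Objective, procedure and outcomes side by side** (sections 1.3, 2.8 and 2.10).

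| Failure of the construct | Primary outcome | Elsewhere in the article |
|---|---|---|
| Flap loss | Only if one of the three signs is scored | Not named |
| Scaffold loss or removal | Only if one of the three signs is scored | Not named; indirectly through bone height, density and volume (secondary) |
| Fixation failure | Only if one of the three signs is scored | Not named; possibly through bone union (secondary) |
| Unplanned re-operation | Only if one of the three signs is scored | Not named |
| Other serious adverse event | Only if one of the three signs is scored | Not named |

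The secondary measures are efficacy measures. A low bone height at a follow-up scan does not enter the safety result, and a patient whose scaffold has been removed may have no later implant measurement at all.

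**Step 2. The plan's own sample size.** Inputs from section 2.6: p = 0.03, margin d = 0.10 (read as an absolute half-width), significance level 0.05 (sidedness not stated).

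n = z² p(1 − p) / d²

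- Two-sided, z = 1.960: 3.8415 × 0.03 × 0.97 / 0.01 = 11.18, rounded up to 12.
- One-sided, z = 1.645: 2.7055 × 0.03 × 0.97 / 0.01 = 7.87, rounded up to 8.

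The stated 10 lies between the two, so it is roughly reproduced and the arithmetic is not the fault. With n = 10 the two-sided half-width is 1.960 × √(0.03 × 0.97 / 10) = 0.106, or 10.6 points.

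**Step 3. What 10 patients can show at 3%.**

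- Expected number of patients with an event: 10 × 0.03 = 0.3.
- Chance of at least one: 1 − 0.97¹⁰ = 0.263, or 26%.
- Exact (Clopper-Pearson) 95% interval: 0 to 30.8% for 0/10, and 0.3 to 44.5% for 1/10.

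Reclassifying a single patient from event-free to event thus moves the upper limit from 30.8% to 44.5%.

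**Step 4. The margin if the event is more common than 3%.** For the same signs and threshold, a wider definition cannot have a lower incidence than the signs alone. The article gives no rate for either, so the rates below are assumptions. Half-width with n = 10: 1.960 × √(p(1 − p)/10).

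| Assumed per-patient incidence | Half-width with 10 patients |
|---|---|
| 3% (section 2.6) | 10.6 points |
| 5% | 13.5 points |
| 10% | 18.6 points |
| 20% | 24.8 points |
| 30% | 28.4 points |

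**The case against.** The strongest reply is that the article condenses a longer clinical investigation plan, to which section 2.12 refers, and that section 2.11 announces a separate SAP. General recording of adverse and serious adverse events is routinely placed there, so nothing shows that a lost flap or a re-operation would go unrecorded. A score threshold and a rule for summarising scores per patient are also details commonly left to those documents. Graft failure would be partly visible in the bone and implant measures. And this is a small pilot with mainly descriptive reporting.

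Most of this stands, and it limits the point to the primary outcome. It does not remove the point. Section 2.10 does not defer the content of the primary outcome; it states which parameters make up the adverse events. Recording a lost flap in a general safety listing would not make it an event in the primary result.

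Three stronger readings are tempting, and the article supports none of them:

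- **That the endpoint is shown not to be the 3% incidence of section 2.6.** Both sections speak of adverse events, and section 2.6 never says which ones the 3% counts. What is visible is repeated scores on one side and a single proportion on the other, with no stated link.
- **That 3% applies to each sign at each visit, so that the per-patient rate is many times higher.** Section 2.6 applies the 3% to subjects. Compounding it over signs and visits would also require independence between repeated looks at the same wound, which nothing in the text supports.
- **That early post-operative inflammation is counted against the graft.** The signs are scored by category and time point, and no text pools the Day 1–10 scores into an event.

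**Conclusion.** The point holds as a mismatch between the primary objective and the primary outcome. As written, a patient with flap loss, scaffold loss or removal, fixation failure, unplanned re-operation or another serious adverse event, and none of the three signs, is event-free on the primary outcome.

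The number of patients affected cannot be estimated, because the article gives no rate for these failures or for how often they occur without a local sign. With 10 patients, each one affected shifts the observed incidence by 10 percentage points.

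The consequence for section 2.6 is conditional. If the 3% is meant for the wider event, the margin with 10 patients stays near the planned 10 points under the normal approximation. If the true incidence is higher, the margin widens as in the Step 4 table; those higher rates are assumptions and do not measure a defect. The conclusion rests on reading the sentence in section 2.10 as the definition of the primary outcome, which is how it is presented.

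**What to change.** Define the primary safety outcome as the proportion of patients with at least one of:

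1. a serious adverse event, flap loss, graft loss or removal, fixation failure or unplanned re-operation through 12 months;
2. inflammation, wound dehiscence or discharging sinus at or above a score that the investigators fix in advance.

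Keep the Day 1–10 signs in the data; excluding them would hide an early dehiscence that is neither serious nor re-operated. Report these signs, and signs that first appear after the 6- and 9-month procedures, by period as well as overall, so that a reader can see what coincides with a procedure.

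In section 2.6, either state that the 3% refers to this event or restate the expected incidence with the margin that 10 patients give. Enrolment need not be increased; the claim about precision should match the event.

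The cost is wording in the protocol and the case report form, with no new visits. Appendix A shows that recruitment has started, so the score threshold should be fixed before the accumulated scores are reviewed. The downside is that the reported primary event rate may be higher, and the stated precision less favourable, than with three signs alone.

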#### Secondary outcome

*Efficacy of NANOTEX BONE graft in supporting Bone Regeneration*: Bone regeneration will be assessed by Cone beam computed tomography (CBCT) assisted by virtual surgical planning and 3D reconstructed stereolithographic models. The radiographic linear measurements will be repeated in the models at each timeline for accuracy and measured in terms of bone height, bone density, bone union, and bone volume during the follow-up scan and its percentage will be measured with the total height.*Efficacy in aiding implant prosthetic rehabilitation*: The resonance frequency analysis (RFA) technique will be used to assess Implant Stability Quotient (ISQ) ranging from 1 (lowest stability) to 100 ISQ units (highest stability). The radiological analysis of the bone-implant area will be done and assessed in terms of bone implant contact, peri-implant radiolucency, and crestal bone loss. Soft tissue will be evaluated in terms of soft tissue recession, dehiscence, bleeding on probing and peri-implant exudation.*Quality of life of the patient*: The patient’s quality of life will be measured by the Liverpool Oral Rehabilitation Questionnaire-17 (LORQ-17), which assesses issues related to oral function, oro-facial appearance, and social interaction. Oral Health Impact Profile 14 (OHIP 14), which refers to prostheses and patient satisfaction with prostheses will be also rated using a 5-point Likert scale.

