## Appendix A

**Table d64e436:**

DATA CATEGORY	INFORMATION

Trial identification number	CTRI/2022/07/044291

Date of CTRI registration	25/07/2022

Sources of monetary or financial support	Biotechnology Industry Research Assistance Council (BIRAC), Govt. of India

Sponsor	Amrita Vishwa Vidyapeetham, Amrita Institute of Medical Sciences, Kochi, Govt. of India

Contact for public queries	[contact]

Contact for scientific queries	[contact]

Study type	Non-randomized Control Trial

Public title	Safety and efficacy evaluation of NANOTEX BONE graft along with fibula flap in reconstruction of the segmental mandibular defect – A Pilot Clinical Trial

Scientific title	A prospective, single-center, non-randomized pilot clinical study to evaluate the safety and efficacy of biodegradable NANOTEX BONE graft (Nanocomposite Fibrous Scaffold) along with fibula flap in reconstruction of segmental mandibular defect due to tumor resection or trauma

Countries of recruitment	India

Intervention	NANOTEX BONE graft

Date of the first patient enrolled	01/08/2022

Recruitment status	Started recruiting

Key inclusion criteria	Age- 18 to 65 years; Segmental mandibular defect due to benign tumor or trauma resection.

Key exclusion criteria	Patients indicated for radiotherapy before and after surgery; Mandibular ramus defects with open wounds; Active uncontrolled infection or malignancy; systemic diseases affecting surgical outcome

Primary outcome	To evaluate the safety of the NANOTEX BONE Graft in combination with fibula flap for bone augmentation

Secondary outcomes	To evaluate the efficacy of the NANOTEX BONE Graft in combination with fibula flap to regenerate new bone in aiding Titanium dental implant placement and integration

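### Visit-by-visit bone readings that also guide implant planning should not be the only efficacy data; a label-free, shuffled re-read of stored scans would reduce expectation bias

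*Protocol article*

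**What the plan says.** The protocol article describes a "Prospective, single-center, non-randomized pilot clinical study" in 10 subjects. Only one intervention is described. The registry table in Appendix A calls the study a "Non-randomized Control Trial", but no control group appears anywhere in the text.

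On the bone outcome, section 2.10 (Secondary outcome) states: "Bone regeneration will be assessed by Cone beam computed tomography (CBCT) assisted by virtual surgical planning and 3D reconstructed stereolithographic models". It continues: "The radiographic linear measurements will be repeated in the models at each timeline for accuracy". The quantities are bone height, density, union and volume.

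The same quantity has a clinical use. Section 2.8 states: "The number and size of titanium dental implants will be planned based on bone gain". Section 2.9 puts implant placement at 6 months, prosthesis placement at 9 months and the end visit at 12 months.

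Section 2.11 compares baseline with later findings by a paired t-test or a Wilcoxon signed-rank test. It names a separate SAP, and section 2.12 refers to a CIP; neither is shown.

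The abstract says of the graft: "We have developed a biomimetic, porous, mechanically stable, and biodegradable nanocomposite". The sponsor's own institute is the only site.

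**The concern.** The efficacy result for bone regeneration is a difference between readings of the same patient at different times. With no concurrent comparator, nothing cancels a tendency to read later scans more favourably than earlier ones. Such a shift goes in full into the paired difference and looks the same as regeneration.

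Three features make this worth guarding against. Bone gain has to be read for implant planning, and for that purpose patient and time point are naturally known. The graft comes from the team running the study, so the expected direction is clear. The one safeguard the article states is a repeat of the linear measurements in the models, which helps with random error but not with an error that both readings share.

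At stake is the first-listed efficacy outcome. It is a secondary outcome: the primary objective is safety, which this point does not touch.

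**Working it through.** **The plan's own figure.** Section 2.6 gives 5% significance, a 3% adverse event rate and a 10% margin of error, and concludes that "the study will be done in 10 subjects to estimate the safety and efficacy with enough precision". The usual precision formula is n = z² p(1 − p) / d².

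- Two-sided 5%: 1.96² × 0.03 × 0.97 / 0.10² = 11.18, rounded up to 12.
- One-sided 5%: 1.645² × 0.03 × 0.97 / 0.10² = 7.87, rounded up to 8.

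The stated 10 lies between the two. This calculation concerns adverse events and says nothing about the bone measurements, so it is used below only as the number of pairs.

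**Where a reading shift goes.** Write δ for the true mean change and b for the mean difference in reading tendency between later and baseline scans. The paired difference then has expectation δ + b. A repeat reading, if averaged, lowers the random part of the variance and leaves b unchanged, so b divided by the SD of the differences does not fall.

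**Inputs**

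- Pairs: n = 10 (section 2.6), all assumed evaluable.
- Test: paired t-test (section 2.11) at 5% (the level in section 2.6, which gives no sidedness), taken as two-sided.
- True change: δ = 0, an assumption made to isolate the effect of b.
- Shift b in SDs of the paired differences: assumed over a range, because the article gives neither an SD of change nor a reader error.

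**Calculation.** The critical value is t(0.975, 9 df) = 2.262, so the result is significant when the mean difference exceeds 2.262 / √10 = 0.715 observed SD. Under a shift b, the test statistic follows a noncentral t distribution with 9 df and noncentrality b√10.

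| Assumed shift (SD) | Noncentrality | Probability of a significant result with no true change |
|---|---|---|
| 0 | 0 | 5.0% |
| 0.125 | 0.40 | 6.5% |
| 0.25 | 0.79 | 10.9% |
| 0.50 | 1.58 | 29.3% |
| 0.75 | 2.37 | 56.2% |
| 1.00 | 3.16 | 80.3% |

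In millimetres this depends wholly on the unknown SD. If the SD of height differences were 0.5, 1 or 2 mm (assumptions), a 0.5 SD shift would be 0.25, 0.5 or 1 mm.

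**Effect of partial masking.** If a masked re-read halved a 0.5 SD shift, the rate would fall from 29.3% to 10.9%. If it halved a 0.25 SD shift, the rate would fall from 10.9% to 6.5%.

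**The case against.** The strongest reply is that the article does not state the fault. Measuring at each timeline says which time points are covered. It does not say who reads the scans, in what order, with which labels, or whether the planning reading is the one analysed. A condensed article may leave this to the CIP or SAP. That stands. A reader might infer that the efficacy readings are unmasked, or that the developers take them, and the document supports neither. The point is therefore conditional: it applies if the visit-linked readings are also the efficacy data.

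Other objections also have weight:

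- The shift sizes are assumed, and the table would fit any 10-pair comparison. This is correct; the table shows sensitivity and is not an estimate for this trial.
- The scaffold itself adds height (section 2.8), so a pre-augmentation baseline would show change without any reader bias, and masking would not alter that. This is correct, and the fix therefore sets the baseline after augmentation.
- Landmark placement bears mainly on linear height, and no separate case is made here for density, union or volume.
- Overstated bone could come to light at implant placement, and implant stability is measured separately by resonance frequency. Both give some independent check, but neither corrects a shifted reading in the bone comparison.
- Masking will be incomplete. Plate, screws and healing stage stay visible, graft size varies between patients, and implants identify later scans.

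These points narrow the claim. They do not remove it, because a visit-linked reading used in a before-after test without a comparator remains open to directional error.

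**Conclusion.** The concern holds in a limited form. If the readings taken at each visit, which also inform implant planning, are the efficacy data, expectation can add to the before-after change, and the stated repeat in the models does not address a shared directional error.

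The size cannot be taken from the document. With 10 pairs, no true change and an assumed shift of 0.25 to 0.75 SD of the differences, the false-positive rate is 11% to 56% instead of 5%.

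A reader might go further and conclude that reader expectation would produce the whole change, or that a masked re-read would abolish the bias. The documents support neither: scaffold height and true regeneration can both contribute to the change, and the scans cannot be fully disguised. The point is an inexpensive improvement to a secondary outcome of a pilot study.

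**What to change.** Leave the visit-by-visit readings as they are for surgical planning. For the efficacy analysis, unless the CIP or SAP already provides for this, add a paragraph to section 2.10 stating that:

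1. the existing reader re-measures the stored post-augmentation, pre-implant cone beam CT scans in one session after data collection, with patient and visit labels removed and the order shuffled;
2. these readings are the ones used in the baseline-to-post comparison of section 2.11;
3. the first post-augmentation scan is the baseline, so that height added by the scaffold itself is not counted as regeneration;
4. scans taken after implant placement are reported separately, because the implant shows the time point.

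The text should say that this reduces expectation bias and does not eliminate it.

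The cost is reader time. No new scan, patient, procedure or reader is needed, the sample size and significance level stay the same, and implant planning is unaffected. The article gives no CT schedule, so the workload is 10 × k scans for k eligible scans per patient. It would be 20 scans if k = 2 and 40 if k = 4 (one each in the surgery period and at 1, 3 and 6 months, an assumption), with several quantities read on each.
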